### Sample size calculation

To our knowledge, no previous study has evaluated the effects of ULAE plus general exercise program compared to general exercise alone among SCI patients, using the RPP (product of SBP and HR) as an outcome. However, since the minimal clinically important difference (MCID) for total Spinal Cord Independence Measure III (SCIM III) has been reported to be 10.0 points [17], this study was powered to detect a minimum difference of 10% points between the ULEA group and control group (assuming a standard deviation [SD] of 12.0, based on the study by Akkurt et al. [15]. Using the following parameters— F-test, repeated measures, between-subjects analysis of variance (ANOVA); alpha (*α*) level of 0.05; power of 0.80; effect size of 0.40 when accounting for 3 repeated measures; and correlation among repeated measures of 0.5— a total of 36 participants was required. Accounting for a potential dropout rate of 30% (n = 10), the final sample size was determined to be 46 participants. Calculations were performed using G Power 3.1.9.2 software [18].

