### Adverse events

All necessary precautions will be taken to prevent the occurrence of any adverse events. Participants will be fully informed of the potential for both serious and non-serious adverse events prior to the commencement of the study interventions. In the event of a serious adverse event (e.g., injuries, persistent excruciating pain, decrease in spine ROM) at any point during the trial, the primary researcher will be immediately notified. The participant may be withdrawn from the study, and appropriate medical care will be sought from a physician. Additionally, reports of serious adverse events will be submitted to the Health Research Ethics Committees of NOHD, AKTH, and Kano State Ministry of Health, Nigeria. Non-serious adverse events that may occur include physical exertion, muscle soreness, dizziness, and exacerbation of muscle or joint pain. These will be monitored and managed appropriately throughout the trial.

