### Data analysis

All statistical analyses will be conducted on IBM SPSS Statistics version 24.0 (IBM Co., Armonk, NY, USA), with a significance level at 0.05.

Descriptive statistics of means and standard deviations will be used to summarize continuous variables, while frequencies and percentages will be used for categorical variables. Data distribution will be assessed statistically using the Kolmogorov–Smirnov and Shapiro–Wilk tests, and visually through histograms, Q-Q plots, and box plots. Baseline comparisons of continuous variables between groups will be conducted using independent *t-*test while the chi-square (χ²) test will be used for categorical variables. For normally distributed data, a mixed model analysis of variance (ANOVA) with a 2 x 3 design (treatment group [ULAE group versus control group] x time [baseline, 8-week post-intervention, and 14-week follow-up]) will be employed to evaluate treatment effectiveness. The treatment group (between-subject factor) will be treated as a fixed effect, while time (within-subject factor) will be treated as a random effect. For non-normally distributed data, the Mann–Whitney *U* test will be used. Potential confounding variables, such as sex, education level, BMI, duration of injury, and type of injury will be adjusted for in the analysis. The intention to treat (ITT) principle will be applied, with all randomized participants included in the analysis according to their originally assigned treatment groups, regardless of whether they completed treatment.

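### The plan promises an ITT analysis of every randomised participant, but the 2 x 3 ANOVA it names, on its usual reading, leaves out anyone missing a visit: 10 to 14 of 46 at the expected dropout

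*Protocol article*

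**What the plan says.** All of the following is in the protocol article.

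- **Data analysis, population.** The ITT principle is to be applied "with all randomized participants included in the analysis according to their originally assigned treatment groups, regardless of whether they completed treatment".
- **Data analysis, method.** Effectiveness is evaluated by "a mixed model analysis of variance (ANOVA) with a 2 x 3 design", with two groups and "time [baseline, 8-week post-intervention, and 14-week follow-up" as the levels of the within-subject factor. Group is a fixed effect, "while time (within-subject factor) will be treated as a random effect". No participant effect and no covariance structure is named.
- **Data analysis, fallback.** "For non-normally distributed data, the Mann–Whitney *U* test will be used".
- **Data analysis, software.** "All statistical analyses will be conducted on IBM SPSS Statistics version 24.0".
- **Sample size calculation.** The trial needs 36 participants and is enlarged to 46: "Accounting for a potential dropout rate of 30" per cent, which the section also writes as 10 people. The Discussion calls the anticipated dropout high.
- **Adverse events.** After a serious adverse event, "The participant may be withdrawn from the study". The section does not say whether the week-8 and week-14 assessments continue.

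**The concern.** The paragraph fixes who is analysed and how, and the two do not fit together. A between/within ANOVA uses each participant's full set of three values. If week 14 is missing, the week-8 value is discarded with it, and a participant with no follow-up disappears altogether. The promised population could then be reached only if nobody missed a visit, yet the trial plans for substantial loss.

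The stakes are the protection that randomisation gives and the accuracy of the label. Readers take ITT to mean that the randomised groups were compared as randomised. A comparison restricted to those seen at all three visits lacks that protection if the reasons for missing a visit are related to outcome. Both primary outcomes (rate pressure product and SCIM III) are affected. There is also a smaller loss of precision, because observed values are thrown away.

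**Working it through.** **1. Does a named method reach the stated population?**

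| Element | What it uses | Participant seen at baseline and week 8 only | Participant seen at baseline only |
|---|---|---|---|
| ITT sentence | all randomised | included | included |
| 2 x 3 between/within ANOVA, standard reading | all three values | excluded | excluded |
| Mann–Whitney U on a follow-up value | observed values at that visit | included at week 8, excluded at week 14 | excluded |

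Neither named method keeps all randomised participants once follow-up is incomplete. The stated random effect does not help. Time here is three fixed visits, and making it random in place of participant does not describe the correlation within a person, which is what lets a mixed model use partial records.

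**2. The plan's own sample size, reproduced.** Inputs from the Sample size calculation section: between-subjects repeated-measures F-test, f = 0.40, m = 3 measures, correlation ρ = 0.5, α = 0.05, power 0.80.

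Noncentrality: λ = f² · N · m / [1 + (m − 1)ρ] = 0.16 × N × 3 / 2 = 0.24N, with 1 and N − 2 degrees of freedom.

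At N = 36, λ = 8.64 and power is 0.815. The smallest N reaching 0.80 is 35, and the smallest even N is 36, so the stated 36 is reproduced.

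**3. How many would be left out?**

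- Dropout as a count: 46 − 10 = 36 analysed, 10 left out (10/46 = 21.7%).
- Dropout as a percentage: 0.30 × 46 = 13.8, so about 14 left out and 32 analysed.

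The two statements of dropout disagree, so both ends are carried forward. The size of the inflation step is a separate matter and is not needed here.

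**4. Power of the protocol's own test at each number.**

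| Participants analysed | λ = 0.24N | Power |
|---|---|---|
| 46 (all with complete data) | 11.04 | 0.901 |
| 36 (10 left out) | 8.64 | 0.815 |
| 32 (14 left out) | 7.68 | 0.765 |

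An analysis using every available visit would fall between the complete-case figure and 0.901. Where it falls depends on when people leave, which the document does not give.

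**The case against.** The strongest reply is that the conflict is inferred. The section speaks of a mixed model and a random effect, and never mentions listwise deletion or complete cases. A likelihood-based fit, which keeps partial records, is compatible with some of those words. This stands as a caveat: a reader might conclude that a completers' analysis is certain, and the text does not establish that. But the paragraph says ANOVA, describes between- and within-subject factors, and makes time rather than participant random, and the trial is sized on a repeated-measures ANOVA. The usual reading is the split-plot ANOVA, and if a linear mixed model was meant, the wording still needs correcting.

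A second reply is that missing-data rules belong in a fuller protocol or SAP. That would answer a complaint that imputation is not mentioned. It does not answer a named method that conflicts with a named population.

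A third is that the ITT sentence concerns stopping treatment, not missing outcomes, and that the adherence section asks participants to complete both follow-up assessments. The final clause does concern treatment, but the sentence opens by placing all randomised participants in the analysis.

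Some stronger inferences are tempting and should not be drawn:

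- **That the allowance for dropout proves a completers' analysis is planned.** Enlarging a sample for dropout is routine under any analysis.
- **That loss will be heavier in the ULAE arm.** That arm has extra session content, but both arms attend three times a week for 8 weeks, and the Adverse events section assigns no event to either arm.
- **That withdrawal after a serious adverse event ends outcome collection.** The section is silent on this.
- **That the bias has a known size.** No document gives the outcomes of those lost, so neither its direction nor its amount can be stated.

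**Conclusion.** The conflict holds on the standard reading of the named method. At the expected dropout, between 10 (the stated count) and 14 (the stated percentage) of 46 randomised participants would be left out, and what is reported as ITT would be an analysis of completers. On the protocol's own test, power would be 0.815 to 0.765, so it is below the 0.80 target only at the 30% end. The loss of power is modest. The main problem is that the label would claim a protection against attrition bias that the method does not give.

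This rests on three assumptions: that the 2 x 3 ANOVA is run in its classical form, that those who drop out each miss at least one of the three visits, and that the protocol's inputs (f = 0.40, correlation 0.5) are taken as given.

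**What to change.** 1. **Replace the ANOVA** with a likelihood-based linear mixed model, which SPSS can fit. Group, time and group-by-time are fixed, with a participant random effect or an unstructured covariance, and all available visits are used.
2. **Keep baseline in the outcome vector**, with its mean constrained to be equal between arms. With baseline as a covariate only, anyone lacking a follow-up value would still fall out. Under the constrained form they enter, though they add little information on the treatment effect, so power is not restored to 0.901.
3. **State the assumption** that the model's validity rests on data being missing at random. Add one delta-adjusted sensitivity analysis for missing SCIM III over a range stated in advance. The 10-point MCID that the protocol cites could serve as a reference point for that range.
4. **If Mann–Whitney is kept**, say whom it includes and do not describe it as an analysis of all randomised participants.
5. **In the Adverse events section, clarify only** that week-8 and week-14 assessments are still sought from participants who stop the intervention, unless consent is withdrawn. This does not touch the decision on when treatment stops.

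The cost is a rewritten analysis paragraph, one extra analysis, and some phone or visit effort to assess people who stop exercising. The analysis changes should be fixed before outcome data are compared by arm. If follow-up has already finished, item 5 can no longer change what was collected, and the report should instead give the number with an outcome at each visit by arm.

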### Data management

Participant data will be recorded in both a logbook and electronically using Microsoft Excel sheets stored on a secure computer hard drive. Prior to data entry, all data will undergo thorough error-checking procedures to ensure accuracy and completeness.

### Dissemination plans

The findings of this study will be disseminated through a knowledge-translation workshop, publication in a peer-reviewed journal, and presentation at a national or international conference.

## Discussion

The management of SCI requires considerable health care resources and can impose a significant financial burden on the affected individuals, their families, and the community [26]. This is particularly concerning in resource-constrained regions, such as northern Nigeria, where many SCI victims come from low-socioeconomic backgrounds [27] and experience low QOL [28], in addition to limited or lack of rehabilitation centers [27,29]. This study aims to determine the effects of ULAE plus general exercise program versus general exercise alone among patients with SCI in northern Nigeria. Based on our hypotheses, we anticipate that participants receiving the ULAE plus general exercise will demonstrate significantly greater improvements in RPP, functional independence, BP, and QOL compared to those receiving general exercise alone. Improvements in these outcomes are expected to help the patients return more quickly to their ADL and maintain an adequate level of physical fitness. The primary strength of this study lies in its design as an RCT with some key methodological features. Additionally, the intervention is both accessible and affordable, as the arm ergometer and reciprocal pulley can be improvised at minimal cost.

However, the study has several potential limitations worth noting. First, due to the nature of the interventions, blinding both participants and therapists will not be feasible. Second, although a formal sample size calculation was performed, the trial is powered to detect only a 10% difference in function, as measured by the SCIM III, between the groups, accounting for the anticipated high dropout rate. Third, due to a lack of funding, only a few outcomes will be evaluated in this trial. Any additional limitations observed during the study will be reported in the main trial publication.

### Trial status

The study opened to participant recruitment on 1 February 2023. The final follow-up is anticipated to be completed by 30 December 2024. The current version of the trial protocol is 6.0.

## Abbreviations:

ADL: Activities of daily living
AKTH: Aminu Kano Teaching Hospital
ANOVA: Analysis of variance
ASIA: American Spinal Injury Association Impairment Scale
BP: Blood pressure
BMI: Body mass index
DBP: Diastolic blood pressure
CVD: Cardiovascular disease
HR: Heart rate
MMSH: Murtala Mohammed Specialist Hospital
NOHD: National Orthopaedic Hospital Dala
RPP: Rate pressure product
SCIM III: Spinal Cord Independence Measure version III
SBP: Systolic blood pressure
SCI: Spinal cord injury
QOL: Quality of life
ULAE: Upper-limb aerobic exercise
WHOQOL-BREF: World Health Organization Quality of Life Scale
